### Study procedures and measurements

#### Qualitative assessment

##### Webinar and Q&A forum

A patient-friendly webinar developed by PLM designed to engage patients and provide avenues for discussion was available on the platform. Topics included an overview of MDD, including symptoms, diagnosis, treatments, tips, management strategies, and an understanding of the PLM platform. It also included an introduction to the GAS-D approach and guidance for patients about when they can request their physician to switch antidepressants. Following the webinar, a Q&A forum was held to encourage additional questions and discussions with the goal of capturing concepts and themes that will improve the quantitative component. The Q&A forum was supported by senior medical advisors from PLM and made available for 7 days to view after the webinar. Patients were contacted through a PLM private message or email for feedback on improving the quantitative component.

##### Usability and functionality testing

Another 10 patients were invited to participate in testing the quantitative survey. The aim was to understand what people with MDD perceive as important reasons for participating in a research study and to learn about their expectations while uncovering pain points, frustrations, and barriers about the overall experience and how they would improve it. This served as a pilot to improve the study design and questionnaires and to contribute to the improvement of the platform itself. Insights gained helped inform PLM about the patient perspective on tools used in the study, including GAS-D, PROs, patient-HCP engagement, and specific questions related to the functionality of the PLM platform to identify strengths and limitations. Evaluation of how participants used the study tool to complete study-specific tasks as well as feedback for suggested changes marked completion of this part of the study. Patients’ expectations for the PLM platform and any suggested platform enhancements make up an important endpoint of the study.

#### Quantitative assessment

##### MDD confirmation

The presence of MDD will be confirmed by reviewing each patient’s diagnostic criteria and current treatment by accessing EMRs through their PLM profile. A directed keyword search will be performed on these records to assess the description and severity of the condition. If a patient does not consent to give access or their condition is not available on EMRs, they have the option to share medical records showing a diagnosis of MDD. Alternatively, they can download the form from the study platform that will allow their clinical practitioner to confirm their MDD diagnosis and antidepressant monotherapy treatment. The PLM team will then look for markers such as disease description to confirm the presence or absence of MDD.

##### Patient demographics and background

Information on patient demographics, symptom characteristics, medical history, and experience with treatment, goal attainment, and communication with their HCP will be collected (Fig. 3).

**Fig. 3 Fig3:**
[figure not shown]
Patient demographics and insights captured during the study. Abbreviations: HCP = healthcare provider; MDD = major depressive disorder; SDM = shared decision-making

##### PLM web-based assessments

Patient measures: A set of surveys including 6 assessment scales will be posted on the PLM platform to capture patient-rated measures of depression, response to therapy using the PGI-I, cognitive functioning using the 5-item Perceived Deficits Questionnaire–Depression (PDQ-D5), QoL using the 5-item World Health Organization Well-being Index (WHO-5), depression severity using the PHQ-9, and life satisfaction using the Quality of Life Enjoyment and Satisfaction Questionnaire–Short Form (Q-LES-Q-SF) (Table 1).

**Table 1 Tab1:** Patient assessments for primary and secondary outcomes

**Primary**	**Patient baseline reflection on current depression status (baselining for PGI-I)**
	**PLM Global Medication Satisfaction Questionnaire**
	• PGI-I Score
**Secondary**	**Subjective Cognitive Impairment**
	• PDQ-D5
	**QoL/Patient Well-being**
	• WHO-5
	**Life Satisfaction Questionnaire**
	• Q-LES-Q-SF
	**Depression Severity**
	• PHQ-9
	**Resilience** ^a^
	• CD-RISC-10
	**Emotional blunting (example questions on Likert scale: Never, Seldom, Not Sure, Sometimes, Always)** ^a^
	• My depression symptoms seem to make me not care about things that I should
	• My current antidepressant treatment seems to make me feel emotionally cut off from my family and friends
	• My current antidepressant treatment dulls my emotions and keeps me from having positive or negative feelings
	**Symptoms of anhedonia** ^**a**^
	• I would enjoy being with family or close friends
	• I would find pleasure in my hobbies and pastimes

^a^Not required, but patients are encouraged to complete

*CD-RISC-10* 10-Item Connor-Davidson Resilience Scale, *PDQ-D5* 5-Item Perceived Deficits Questionnaire–Depression, *PGI-I* Patient Global Impression of Improvement, *PHQ-9* 9-item Patient Health Questionnaire, *PLM* PatientsLikeMe, *Q-LES-Q-SF* Quality of Life Enjoyment and Satisfaction Questionnaire–Short Form, *QoL* quality of life, *WHO-5* 5-Item World Health Organization Well-being Index

In addition, sections with questions related to background, emotional blunting, anhedonia, and resiliency will also be available; however, completion of this section and goal tracking are not required for patients but rather encouraged.

Platform goal tracking: After baseline assessments, patients will be asked to create up to 3 specific, measurable, achievable, realistic, and time-bound (SMART) goals on the PLM platform using the GAS-D approach. Educational videos on how to set and track goals will be available throughout the study period. Patients will track the progress of their goals every week and will be able to see their aggregated goal progress. After 12 weeks, patients will be asked to provide final progress updates on the 3 goals they set for goal attainment calculations. Then they will be asked to set 3 new goals or to update previous goals to track from week 12 to week 24.

#### Data collection, management, and statistical analyses

Patient demographic data will be collected at baseline, and the web-based assessment data and some background data will be collected at weeks 12 and 24. The schedule for these evaluations is presented in Table 2. Final analytic datasets, with no individual identifying information, will be shared with the study collaborator for future analytic use. Any publication or presentations of the results from the research will include only aggregated, deidentified information.

**Table 2 Tab2:** Schedule of evaluations

**PLM-MDD** **Schedule of Evaluations**	**Screening and Webinar**	**MDD Forum**	**User Experience**	**Screening**	**Baseline**	Weeks 1–5	Week 6	Weeks 7–11	Week 12	Weeks 13–17	Week 18	Weeks 19–23	Week 24
						+6 days	+6 days	+6 days	+6 days	+6 days	+6 days	+6 days	+10 days
**Qualitative Component**													
Screening and webinar invites	**X**												
Webinar	**X**												
Screening and invites	**X**												
Qualitative consent		**X**	**X**										
Q&A forum		**X**											
Useability and functionality insights			**X**										
**Quantitative Component**													
**Background and Insights**													
Screening and invite emails				**X**									
Consent					**X**								
MDD diagnosis confirmation					**X**^**a**^								
Demographics (age, sex, race, ethnicity, weight, height, employment status, insurance class)					**X**								
Comorbidities					**X**								
Antidepressant treatment experience					**X**								
Characterization of symptom experience importance and patterns					**X**				**X**				**X**
Patient experiences: goals and HCP communication					**X**				**X**				**X**
Current antidepressant medication					**X**				**X**				**X**
**PLM Web-Based Assessments**													
PHQ-9				**X**			**X**		**X**		**X**		**X**
Baseline reflection on current depression status					**X**								
PGI-I									**X**				**X**
Q-LES-Q-SF					**X**				**X**				**X**
PDQ-D5					**X**				**X**				**X**
WHO-5					**X**				**X**				**X**
Emotional blunting questions					**X**				**X**				**X**
SHAPS questions					**X**				**X**				**X**
CD-RISC-10					**X**				**X**				**X**
Goal setting/tracking questions					**X**				**X**				**X**
Goal setting					**X**				**X**				
Goal attainment tracking						**X**	**X**	**X**	**X**	**X**	**X**	**X**	**X**
Goal attainment scale for depression									**X**				**X**

^a^6 weeks for MDD confirmation

*CD-RISC-10* 10-Item Conner-Davidson Resilience Scale, *HCP* healthcare provider, *MDD* major depressive disorder, *PDQ-D5* 5-item Perceived Deficits Questionnaire–Depression, *PGI-I* Patient Global Impression of Improvement, *PHQ-9* 9-item Patient Health Questionnaire, *PLM* PatientsLikeMe, *Q&A* question-and-answer, *Q-LES-Q-SF* Quality of Life Enjoyment and Satisfaction Questionnaire–Short Form, *SHAPS* Snaith-Hamilton Pleasure Scale, *WHO-5* 5-item World Health Organization Well-being Index

For the qualitative analysis, themes arising from any free-text data were qualitatively evaluated and presented as frequencies in tables using a directed content analysis approach. A coding system for thematic analysis was created by PLM team members. The quantitative analysis will be summarized using descriptive statistics for patient characteristics by age, sex, condition-related characteristics, and treatments. For continuous variables, descriptive statistics will include the number of observations (N), mean and SD (mean, SD), median and interquartile range (median, [Q1, Q3]), and minimum and maximum values (min, max). For categorical variables, descriptive statistics will include the frequency and relative percentage of values in each category. Upon review of data, chi-square statistics will be used for categorical variables, while two sample *t*-tests and the analysis of variance procedure will be used to assess continuous variables between/among groups. To address confounding, various methods used in observational studies, such as stratification, corresponding to the levels of potential confounders (e.g., age groups and sex) will be employed as applicable. A multivariable regression analysis also will be used to control confounding. A total of 480 patients are planned to be recruited, to have at least 378 patients complete the week 12 survey after accounting for 15% of responders at week 12 (PGI-I < 2) and 20% attrition.

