### Rationale and aim of the study

In this ongoing, observational, real-world, prospective, decentralized study, we aim to gain insight and better understanding of the treatment experience of patients living with MDD, including symptom management, side effects, medication switches, and any treatment goals. Patients are provided with assessments within the PLM platform that support MBC, potential SDM, and tools to help them track their health-related goals, such as mood, cognitive symptoms, emotional well-being, and function. The primary objective of the study is to assess Patient Global Impression of Improvement (PGI-I) scores with vortioxetine at 12 weeks compared with other monotherapy antidepressant treatments following a new start or switch. Secondary objectives include measurement of changes between groups in MDD symptoms and severity, cognitive function, well-being, emotional blunting, resiliency, medication satisfaction, QoL, goal attainment, and patient engagement using the PLM platform. Additional areas of exploration will focus on aspects of the patient journey, such as medication adherence, reason for switching medication, compliance, and barriers to treatment.

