### Quantitative study

Three quantitative surveys at baseline, week 12, and week 24 will be conducted to collect the data. The quantitative survey uses the PLM platform to track important health information such as mood, well-being, cognitive impairment, function, QoL measures, and goal attainment. This platform also consists of patient-facing educational support and videos to set and track patient goals with their HCPs. A doctor visit guide is available for patients so they can relay important health information, as well as their goals and PROs, from the PLM platform to their care team, either electronically or face-to-face.

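### The tests named for the secondary outcomes neither adjust for the entry score nor use intermediate visits, and the adjusted regression is not specified as the main secondary analysis

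*Protocol article*

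**What the plan says.** In the protocol article, Rationale and aim of the study frames the secondary aims as change: "Secondary objectives include measurement of changes between groups in MDD symptoms and severity, cognitive function, well-being", followed by further patient-reported domains.

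Quantitative study describes repeated measurement: "Three quantitative surveys at baseline, week 12, and week 24 will be conducted to collect the data". Table 2 adds PHQ-9 at weeks 6 and 18, so PHQ-9 is taken five times (screening, weeks 6, 12, 18 and 24). Q-LES-Q-SF, PDQ-D5, WHO-5 and CD-RISC-10 are taken at baseline, week 12 and week 24.

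Data collection, management, and statistical analyses names the between-group tests. For categories, "chi-square statistics will be used for categorical variables". For continuous measures, two-sample t-tests and ANOVA: "the analysis of variance procedure will be used to assess continuous variables between/among groups".

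The same section then turns to confounding. It mentions methods "such as stratification, corresponding to the levels of potential confounders (e.g., age groups and sex) will be employed as applicable", and says "A multivariable regression analysis also will be used to control confounding". It does not give the regression's outcomes, covariates or visit structure. The entry score is not named as a confounder.

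Table 1 gives the emotional blunting items as "example questions on Likert scale: Never, Seldom, Not Sure, Sometimes, Always", without a scoring rule.

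**The concern.** The groups are formed by treatment choice, and the Limitations section concedes confounding by selection and indication. Entry severity is an obvious candidate for imbalance. A two-sample t-test, on scores or on change, does not condition on the entry score. If both groups drift toward a common mean, part of any entry gap appears as a difference between drugs even when there is none.

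The named tests also leave collected data unused. A week-12 comparison by t-test makes no use of PHQ-9 at week 6, and a week-24 comparison none of week 18. The article plans for 20% attrition, which is 0.20 × 480 = 96 of those recruited. Any of these patients with a week-6 but no week-12 score contributes nothing to a week-12 t-test.

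Finally, an unordered chi-square on a five-level item spends four degrees of freedom on what is usually a shift in one direction.

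**Working it through.** **Inputs from the article.** 378 patients evaluable at week 12 with a 2:1 recruitment ratio (Study population): 378/3 = 126 on vortioxetine and 252 on other monotherapy, if the ratio holds among evaluable patients.

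**Inputs assumed.** The article gives no SD, correlation, entry gap, effect size or alpha, so it has no figure of its own to reproduce on this point. I assume two-sided alpha 0.05, PHQ-9 SD 5 at each visit, entry-to-follow-up correlation r = 0.5 (varied below), and entry gaps of 0.5 to 2 points.

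**1. Efficiency.** In units of the single-visit variance:
- change score: 2(1 − r)
- baseline-adjusted: 1 − r²
- ratio: 2/(1 + r)

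At r = 0.5 this is 1.00 against 0.75, a ratio of 1.33. At r = 0.4 the ratio is 1.43 and at r = 0.6 it is 1.25. The change-score t-test therefore has 25% to 43% more variance, which is equivalent to needing that many more patients.

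Power for a 0.3 SD difference:

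| r | t-test on change | Baseline-adjusted |
|---|---|---|
| 0.3 | 64% | 82% |
| 0.5 | 79% | 89% |
| 0.7 | 94% | 97% |

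**2. False positives from an entry gap, no drug effect.** If scores regress to a common mean, the expected difference in change has size (1 − r) × gap. The standard error is 5 × √(2(1 − 0.5)) × √(1/126 + 1/252) = 0.546 points.

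| Entry gap (points) | Expected spurious difference | Divided by SE | Rejection rate |
|---|---|---|---|
| 0.5 | 0.25 | 0.46 | 7% |
| 1.0 | 0.50 | 0.92 | 15% |
| 1.5 | 0.75 | 1.37 | 28% |
| 2.0 | 1.00 | 1.83 | 45% |

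For the 1-point gap (0.2 SD), the rate on change scores is 19%, 15% and 11% at r = 0.3, 0.5 and 0.7. On single-visit scores it is 8.5%, 15% and 25%. Taking change does not remove the problem. A baseline-adjusted model holds 5% if it is correctly specified.

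**3. Ordered items.** Simulated power with 252 and 126 patients, proportional odds, and an assumed reference distribution of 15/20/20/30/15% (2,000 runs):

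| Odds ratio | Chi-square | Rank test | t-test on scores |
|---|---|---|---|
| 1.5 | 34% | 54% | 54% |
| 1.75 | 63% | 84% | 84% |
| 2.0 | 82% | 93% | 93% |

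The loss occurs only if chi-square is applied to the ordered categories. Scoring the answers keeps the order.

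**The case against.** The strongest reply is that this is a condensed article, with an analysis plan available on request, and that covariate lists, visit modelling and item scoring belong there. That stands for the covariate list. It does not fully answer the point, because the article itself chose the test families, and they suit this objective and schedule poorly.

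Three stronger readings are tempting, and the article does not support them:

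- *Each visit is analysed as a separate cross-section.* The article does not say what the t-test is run on. The objective speaks of change, and a t-test can be run on change scores.
- *Likert answers are treated as unordered.* Chi-square is assigned to categorical variables, and the article does not say that these items are classed that way. A middle answer of not sure also makes their ordering open to question.
- *The plan as a whole would pass an entry gap off as a drug difference.* Stratification and multivariable regression are planned, and age and sex are only examples. The regression could include the entry score.

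Two further objections stand. In a non-randomised comparison, if the groups differ stably in level and do not regress to a common mean, change scores can be unbiased and baseline adjustment biased (Lord's paradox); the rejection rates above would then not apply. And the inclusion criteria let the start or switch precede consent by as much as 90 days, so the entry score may already carry drug effect that adjustment would partly remove.

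**Conclusion.** The point holds in a limited form and merits a change to the secondary analysis. The named tests do not adjust for the entry score or use PHQ-9 at weeks 6 and 18. The regression that could adjust for it is neither specified nor named as the main secondary analysis.

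Under the assumed inputs, the unadjusted change-score t-test carries 25% to 43% excess variance and a false-positive rate of 7% to 45% for entry gaps of 0.5 to 2 points. The 45% is the top of that range and needs a gap of 0.4 SD. The loss on Likert items, about 11 to 21 percentage points of power, is conditional on chi-square being used for them. None of these figures describes a regression that includes the entry score, and none can be confirmed from the article because it gives no SD, correlation or expected gap. The point concerns secondary outcomes only.

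**What to change.** In Data collection, management, and statistical analyses:

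1. State that the adjusted model is the main secondary analysis, and keep unadjusted t-tests and chi-square as descriptive.
2. For PHQ-9, PDQ-D5, WHO-5, Q-LES-Q-SF and CD-RISC-10, use a repeated-measures mixed model with entry score, drug group, visit, group-by-visit interaction and the chosen confounders. Use all scheduled visits, and report the week-12 and week-24 contrasts with confidence intervals.
3. For single Likert items, use a rank or proportional-odds method, or a stated scoring, instead of an unordered chi-square.
4. Include time since start or switch as a covariate, and report an analysis without entry-score adjustment as a sensitivity check.

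The cost is wording and modest programming; no assessment is added to the schedule. The mixed model relies on data being missing at random, and the ordinal model on proportional odds; the latter can be checked in the data, the former only probed by sensitivity analysis. Entry-score adjustment may still absorb some early drug effect, which is why item 4 is needed.

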## Results

The webinar, Q&A forum, and qualitative component of the study have been completed, and completion of the quantitative component is scheduled for September 2023. The webinar received > 2000 clicks and > 200 views. The 10 patients enrolled for the usability testing were women aged 51 to 80 years. Results will be available in subsequent publications and are expected to provide insights into treatment experiences such as improvement in symptoms, cognitive ability, treatment satisfaction, emotional blunting, anhedonia, and overall well-being with vortioxetine versus other SOC monotherapy from a patient perspective in a real-world setting in patients with MDD. The goal achievement approach will shed light on how patients perceive their treatment goals and will help identify the improvements that are most meaningful to them. Another focus of this study will be to gain feedback from patients on how they perceive various functionalities on the PLM platform, such as sharing health data with HCPs and how this can be further improved to benefit patients. Thus, features such as goal setting and tracking may evolve to be permanently included as a function on the PLM platform, depending on patient feedback. Some study features may advance to become permanent PLM platform components based on results of the interest and engagement patients show in setting and tracking their goals and the feedback provided during functionality testing.

## Discussion

We believe that the methodology of this study can add value to the MDD community because of its unique design that uses a combination of patient education, surveys, and a set of quantitative assessments captured with PROs. The outcomes of this study will be patient-driven, and as it is hosted on the PLM platform, the data can offer real-world evidence, representing the population in a clinical setting. In addition, by using the goal-setting and goal-tracking approach in this study, we can better understand what patients with MDD consider to be their goals in recovery. Thus, key insights can be gained into patient perspectives of improvement in their daily functioning and well-being.

PLM is an online patient community that serves as a repository for patient-produced data, leveraging the power of social networking among patients with chronic, life-changing conditions [28]. The platform provides patients with resources to explore their condition, share experiences with peers, track their symptoms, identify treatment options, and share outcomes, thereby improving overall quality of care [23]. Digital platforms such as PLM provide patients with MDD with a greater understanding of the disease and can potentially improve outcomes in this population as a result of informed treatment decisions and improved medication adherence [21]. For patients with MDD, deidentified, computable data obtained through the PLM platform can be an effective measure of PROs, patient perspectives, and preferences [28]. Research studies conducted on PLM have the potential to be patient focused, as they capture patient-centric information and are easy to participate in because they are virtual.

The PLM platform enables the conduct of observational studies, which play a vital role in investigating treatment outcomes. In the primary care setting, observational studies help to inform SDM and patient engagement in their treatment [29]. The prospective design of this study will provide insights into the effectiveness of vortioxetine compared with other SOC treatments, as well as the use of digital technology for patient support in a real-world setting [30].

To fully understand goals and meaningful outcomes for patients with MDD, it is vital to identify the challenges that they face in the course of their treatment. Patients with MDD seeking treatment often experience improvement in symptoms related to mood much later than improvements in physical and cognitive symptoms. Some of the main reasons for treatment discontinuation cited by patients with MDD are lack of remission, low tolerability, and minimal engagement with their HCPs [31]. A majority of patients with MDD report residual functional impairment, which does not lead to long-term recovery [15, 32]. In the real-world RELIEVE study, vortioxetine was found to be safe and effective in improving functioning and treatment adherence in clinical practice. Patients also experienced clinically relevant improvements in depressive symptoms, cognitive symptoms and performance, and health-related QoL over the 6-month treatment period [33].

Further expanding on existing evidence, this study aims to provide data supporting patients’ perspectives of MDD symptom improvement and will assess patient-centric outcomes for mood, cognitive symptoms, emotional well-being, medication satisfaction, QoL, and goal engagement in new start-and-switch patient populations with long-term use of vortioxetine versus other SOC monotherapy. For patients with MDD, PROs can accurately represent clinical status, especially for the maintenance of long-term disease [34]. The PRO assessments used in this PLM study for symptom improvement (PGI-I), subjective cognitive impairment (PDQ-D5), treatment satisfaction (Q-LES-Q-SF), and depression severity (PHQ-9) can provide substantiating evidence for the use of these scales. The outcomes of this PLM study will help to elucidate the importance of patient engagement with HCPs and may provide a better way to develop tools for patients to be able to track, share, and be in control of their condition and treatment. By incorporating a patient-reported, goal-based approach, we aim to understand how receptive patients with MDD are to setting and sharing their goals with HCPs [35]. The evidence for the benefit of SDM and MBC for meaningful treatment outcomes in patients with MDD will be the cornerstone of this study.

